#### Space from depression

The online intervention ‘*Space from Depression*’ is a seven-module online CBT-based intervention for depression, delivered on a Web 2.0 platform using media-rich interactive content. Programme content is delivered in a non-linear fashion. Each module takes roughly 1 h to complete, and it is recommended one module be completed per week. The structure and content of the programme modules follow evidence-based CBT principles. The treatment is comprised of established cognitive and behavioural components including self-monitoring, self-control desensitisation, gradual stimulus control, thought recording, behavioural activation, cognitive restructuring, relaxation training and challenging core beliefs. In addition, given the frequent comorbidity of depression with anxiety symptoms, the platform provides PWPs with an option to deliver a mixed programme comprising the core depression modules delivered alongside a module about worry management. Each module is structured to incorporate introductory quizzes, videos, informational content, interactive activities, as well as homework suggestions and summaries. In addition, personal stories and accounts from other users are incorporated into the presentation of the material. The intervention follows NICE guidelines for the treatment of depression and the intervention has been tested and proved efficacious [10, 11, 38].

#### Space from anxiety

The online intervention ‘*Space from Anxiety’* is a seven-module online CBT-based intervention for anxiety, delivered on a Web 2.0 platform using media-rich interactive content. Programme content is delivered in a non-linear fashion. Each module takes roughly 1 h to complete, and it is recommended one module be completed per week. The structure and content of the program modules follow established evidence-based principles of CBT for the treatment of anxiety disorders. The treatment comprises cognitive, emotional, and behavioural components that include self-monitoring, relaxation training, cognitive restructuring, and worry outcome monitoring. The intervention also delivers customisations to modules based on the different anxiety disorder presentations, for example, in social anxiety the modules include attention control and the personal stories are of individuals experiencing social anxiety. The getting started module for the core anxiety programme introduces the user to the cycle of anxiety and the emotional, cognitive and behavioural aspects of anxiety. The goal of the intervention is to help people with anxiety as a primary disorder manage their thoughts, emotions and behaviours to help them alleviate their symptoms. The intervention follows NICE guidelines for the treatment of anxiety [10, 11].

#### Waiting list control group

Participants in the waiting list control group receive no treatment for the duration of the first 8-weeks. At week 8, waiting-list participants will complete the primary and secondary outcome measures and begin their treatment with support from a PWP.

#### Support during treatment

Each participant will be assigned a PWP clinician who will monitor participants’ progress throughout the trial. Once assigned to the active treatment condition the participant will receive a message from their PWP clinician at their first login. This message welcomes them to the program, highlights aspects of the program, and encourages them in use of the program. Over the course of the 8-week supported intervention, on 6 separate occasions the PWP will login and review participants progress, leaving feedback for them and responding to the work they have completed. The basic share level allows supporters to view users’ goals for the week, key messages and progress points. If users wish to share more with their supporter, they can share journal entries. Each supporter will provide post-session feedback of between 10 and 15 min per participant per session, over the eight-week intervention period.

Supporters will be supervised by case managers, who are responsible for monitoring fidelity of the PWP to the content of the specific iCBT intervention. At each supervision meeting they will complete a fidelity checklist. The checklist is an assessment of the congruence between the content of the PWP’s online reviews and the CBT module that the client is progressing through. This will ensure that patients receive the appropriate evidence-based intervention and that each client receives a similar standard of intervention, augmenting the reproducibility of the study. Furthermore, the trial steering group will meet weekly with PWP managers to audit the trial conduct, its processes and overall progress.

### Measures

#### M.I.N.I. International neuropsychiatric interview 7.0 (MINI) [37]

The current version is 7.0 and is based both on the Diagnostic and Statistical Manual of Mental Disorders (DSM-5) and the International Classification of Diseases (ICD-10) criteria. The interview has been well validated and the administration of the interview by telephone has been validated. The Interview schedule will include the following modules: Module A (Major Depressive Episode), Module D (Panic Disorder), Module F (Social Anxiety Disorder), and Module N (Generalized Anxiety Disorder), in order to establish current depression and anxiety and specific anxiety presentations. For research purposes randomisation to either *Space from Depression* or *Space from Anxiety* will be based on the outcome from the M.I.N.I. In the event where a clear diagnosis is not available the clinician will decide on the diagnosis based on the outcome from the M.I.N.I. and clinical knowledge from the initial assessment (scores on the PHQ-9, GAD-7).

##### Primary outcome measures

ᅟ

#### Patient health Questionnaire-9 (PHQ-9) [39, 40]

The PHQ-9 is a self-report measure of depression that has been widely used in research and is a regular screening measure utilised in primary care and hospital settings. The PHQ-9 items reflect the diagnostic criteria for depression outlined by the Diagnostic and Statistical Manual of Mental Disorders, Fourth Edition – Text Revision (DSM–IV–TR) [41]. Summary scores range from 0 to 27, where larger scores reflect a greater severity of depressive symptoms. The PHQ-9 has been found to discriminate well between depressed and non-depressed individuals using the cut-off total score ≥ 10, with good sensitivity (88.0%), specificity (88.0%) and reliability (89, 39).

#### Generalized anxiety Disorder-7 (GAD-7) [42]

GAD-7 comprises 7 items measuring symptoms and severity of anxiety based on the DSM-IV diagnostic criteria for GAD. The GAD-7 has good internal consistency (α = .92) and good convergent validity with other anxiety scales [42]. Higher scores indicate greater severity of symptoms. The GAD-7 has increasingly been used in large-scale studies as a generic measure of change in anxiety symptomatology, using a cut-off score of 8 [43].

##### Secondary outcome measures

ᅟ

#### Diagnosis-specific measures

Participants with a principal diagnosis of anxiety and of specific anxiety including social anxiety, GAD, panic disorder or health anxiety will also complete the associated anxiety disorder specific measure depending on their main diagnosis.

##### IAPT phobia scales

The IAPT Phobia scales have been designed with the aim of capturing patients who may score below the clinical cut-off on the PHQ-9 and GAD-7 but whose lives may be significantly impaired by the presence of social anxiety, agoraphobia and specific phobias [44].

##### Social Phobia Inventory (SPIN) [45]

Consisting of 17 self-rated items for social anxiety disorder, this test asks the user to reflect over the past week and report on their experiences as laid out by the inventory, which assesses the domains of social anxiety disorder (fear, avoidance and physiological arousal). Scores are then totaled to produce a value that is representative of symptom severity on a continuum from none to very severe. Internal reliability for the SPIN has been placed at α = .95, with α values for the subscales ranging from .79–.85. [45].

##### Short Health Anxiety Inventory (HAI) [46]

This scale measures levels of health anxiety, which is characterised by the misinterpretation of bodily sensations as a serious illness. The shortened version of the scale has been constructed such that it is sensitive to both normal and severe levels of health anxiety. A meta-analysis of the inventory has yielded α values between .74–.96 [47].

##### Panic Disorder Severity Scale-Self Report (PDSS-SR) [48]

This scale measures severity of panic disorder and is considered a reliable tool in treatment outcome studies. It consists of seven items rated on a 5-point scale that ranges from 0 to 4. The items assess panic frequency, distress during panic, panic-focused anticipatory anxiety, and phobic avoidance of situations, phobic avoidance of physical sensations, impairment in work functioning, and impairment in social functioning. The total sum of the individual scores ranges from 0 to 28, where higher scores indicate greater severity. A score of 9 or above is indicative of caseness. It has displayed good psychometric properties [49].

##### The Penn State Worry Questionnaire (PSWQ) [50]

This questionnaire consists of 16 items and is considered a valid clinical measure of the worry characteristic of GAD. Each item is measured on a 5-point Likert scale (1 – not at all typical of me to 5 – very typical of me) and a total score ranging between 0 and 80 is calculated by summing all items. Psychometric evaluations have revealed a high internal consistency (α = 0.86 to 0.95) and test-retest reliability over four weeks (*r* = 0.74 to 0.93) [51]. The measure has also been found to successfully differentiate between patients with GAD and those with other anxiety disorders [52].

#### Functional impairment

##### Work and Social Adjustment (WSAS) [53]

This is a simple, reliable and valid measure of impaired functioning. It is a 5-item self-report measure that provides an experiential impact of a disorder from the patient’s point of view. It looks at how the disorder impairs the patient’s ability to function day to day on five dimensions: work, social life, home life, private life and close relationships.

#### Cost effectiveness

##### EuroQoL Five Dimension Five Level Version (EQ-5D-5 L) [54]

This measure is used to assess a person’s perception of their general health state and obtain a measure of quality adjusted life years (QALYs). Outcomes can be benchmarked against UK population norms. It covers five dimensions: mobility, self-care, usual activity, pain/discomfort and anxiety/depression, which are rated by the person on five levels of severity: no problems, slight problems, moderate problems, severe problems and extreme problems/unable to function within that domain.

##### Recovering Quality of Life – 10 item version (ReQoL-10) [55]

This recently developed measure is used to assess a person’s perception of their generalised mental well-being which is associated with recovering quality of life. The measure focuses on seven key themes associated with recovering quality of life: well-being; autonomy, control, choice; self-perception; relationships and belonging; hope; activity; physical health. It is composed of 10 questions (with one additional question focused on physical health) rated on a 5-point scale which describes a persons thoughts, feeling and activities over the last week.

##### Client Service Receipt Inventory (CSRI) [56]

This collects individuals’ use of health and social care resources. It comprises questions about health care utilization including inpatient and outpatient hospital services, community-based day services, primary and community care contacts and employment status. This version of the CSRI is routinely administered at the study site.

#### Satisfaction with treatment measures

##### Patient Experience Questionnaire (PEQ) [44]

This instrument will be used to assess patient experience and satisfaction. The PEQ contains several quantitative questions and open-ended questions that are used to assess participant’s views and satisfaction with service provision.

#### Mechanisms of change and maintenance

##### Scale to Assess Therapeutic Relationship – Patient version (STAR-P) [57]

This scale will be employed to assess patients’ experiences of the therapeutic relationship online. It will be administered to patients throughout treatment following each progress review with the clinician.

##### Scale to Assess Therapeutic Relationship – Clinical version (STAR-C) [57]

This will be employed to assess clinicians’ experiences of the therapeutic relationship online. The measure will be administered each time the clinician writes a review for their clients.

##### Positive Beliefs about Rumination Scale – Adapted Version (PBRS-A) [58]

This scale has 9 items that measure positive beliefs about repetitive negative thinking. Participants complete each item using a 4-point scale, 1 = *do not agree* to 4 = *agree very much*. The measure has good internal reliability (α = .89).

##### Emotion Regulation Questionnaire (ERQ) [59]

The ERQ is a 10-item scale that assesses individual differences in the habitual use of two emotion regulation strategies: cognitive reappraisal and expressive suppression. Each item is rated on a 7-point scale so that higher scores indicate higher use of reappraisal/ suppression. This scale has shown appropriate levels of internal reliability on both subscales, reappraisal and suppression (0.79 and 0.73, respectively).

##### Frequency of Actions and Thoughts Scale (FATS) [60]

The FATS is a 12-item scale, designed to assess the frequency with which CBT-related skills have been used during the previous week. Each item is measured on a 5-point scale (0 = not at all, 1 = one or two days; 2 = half the days; 3 = almost every day; 4 = every day). The FATS comprises four subscales, indicative of how much the person engaged in 1) cognitive restructuring, 2) social interaction, 3) rewarding behaviours and 4) activity scheduling in the past week; but also gives an overall score, indicative of overall CBT-related skills usages. Psychometric evaluations suggest high internal consistency of the total FATS scale (α = 0.86) and acceptable to high internal consistency of its subscales (α = 0.74 to 0.83). The FATS has been shown to be sensitive to change during iCBT and higher scores on the FATS have been linked to better treatment outcomes.

##### Psychological wellbeing practitioner behaviours checklist

A checklist of behaviours based on existing literature has been developed to assess the behaviours used by PWPs in their communication with patients. The checklist is based on known therapist behaviours and the items have been evaluated by PWPs for relevance. It will be an optional function within the SilverCloud platform that PWPs will be invited to complete each time they communicate with their patient.

##### Expectancy/credibility questionnaire

This is a one question item that assesses the clients level of credibility with the intervention and is based on the work in this area [61].

#### Dropout measure

Finally, a *dropout questionnaire* will assess participants’ reasons for dropout from treatment. It includes only one open question asking for details about the specific reasons for dropout.

The study measures and assessment times are summarised in Table 2.

**Table 2 Tab2:** Study measures and assessment times

Measure	Assessment	Time of assessment
M.I.N.I. 7.0.2 for DSM-5	Diagnosis	BL and 3-FU
PHQ-9	Depression	BL, contin, Post-T, FU
GAD-7	Anxiety	BL, contin, Post-T, FU
IAPT Phobia Scale	Specific Phobia	BL, contin, Post-T, FU
WSAS	Functioning	BL, contin, Post-T, FU
SPIN	Social Phobia	BL, Post-T, FU
HAI	Health anxiety	BL, Post-T, FU
PSWQ	GAD	BL, Post-T, FU
PDSS	Panic	BL, Post-T, FU
EQ-5D-5 L	Health status	BL, Post-T, 6-FU, 9-FU, 12-FU
ReQol-10	Recovering quality of life/ mental wellbeing	BL, Post-T, 6-FU, 9-FU, 12-FU
CSRI	Resource utilisation	BL, Post-T, 6-FU
PEQ	Patient experience	Post-T
STAR-C	Therapeutic alliance	Throughout treatment, at each review of client
STAR-P	Therapeutic alliance	Throughout treatment, after each progress review with clinician
PBRS-A	Repetitive Negative Thinking	BL, week 4, Post-T, 3-FU
ERQ	Emotion Regulation	BL, Post-T
FATS	CBT-related skills usage	FU
Therapist behaviours checklist	Therapist behaviours	During treatment at review of client
Expectancy / credibility	Expectancy and credibility with the intervention	BL, week 4, Post-T
Dropout questionnaire	Reasons for dropout	3-FU

*BL* Baseline, *Post-T* Post-Treatment, *FU* All follow-ups, *3-FU* 3-month follow-up, *6-FU* 6-month follow-up, *contin* continuous, *PHQ-9* Patient health questionnaire-9, *GAD-7* Generalized anxiety disorder-7, *WSAS* Work and social adjustment, *SPIN* Social Phobia Inventory;` *HAI* Short health anxiety inventory, *PDSS* Panic disorder severity scale-self report, *PSWQ* Penn state worry questionnaire, *EQ-5D-5 l* EuroQol-5 Dimension-5 level, ReQoL-10 Recovering quality of life – 10 item version, *CSRI* Client services receipt inventory, *PEQ* Patient Experience questionnaire, *PBSR-A* Positive Beliefs about Rumination Scale – Adapted Version, *FATS* Frequency of Actions and Thoughts Scale, *ERQ* Emotion Regulation Questionnaire

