Resource-use and subsequent costs will be estimated over the 12-month time horizon for the intervention group and for the 8-week waiting list time period for the control group. Healthcare resource will be valued using unit costs derived from available data sources [62–66].

For the purpose of the economic evaluation, EQ-5D-5 L and ReQoL-10 preference-based tariff score values will be used to elicit the quality adjusted life year (QALY) using the area under the curve (AUC) method to account for the collection of this data at multiple time points between baseline and 12-month follow-up in both trial-arms. The proposed economic analysis will be conducted for those with anxiety and those with depression separately and as a whole patient group. All economic analysis will be performed using Stata version 14 (or an updated version). Due to the shorter time horizon of the control groups (8 weeks based on a waiting list approach) compared to the intervention group (12 months with outcome assessment at 8 weeks, 6 months, 9 months and 12 months), methodological work will be carried out to assess the feasibility and uncertainty around extrapolating outcomes from the 8-week time period in the control group to a longer time horizon (e.g. 6-months, 9-months and 12-months) using survival analysis methods [67]. Cost per QALY analysis will be carried out over multiple time horizons (e.g. 8-weeks, 6-months, 9-months and 12-months) to address the uncertainty around decision making from using observed data (up to 8 weeks) and extrapolated outcomes (beyond 8 weeks) for the economic evaluation. Incremental mean point estimates of the difference in cost and QALYs between trial groups will be used to determine the incremental cost effectiveness ratio (ICER). ICER is defined here as the ratio between incremental costs and incremental effectiveness and the following formula will be employed:$$ ICER=\frac{\mathrm{Cost}\kern0.5em \mathrm{active}\kern0.5em \mathrm{intervention}\kern0.5em \mathrm{group}\hbox{-} \mathrm{Cost}\kern0.5em \mathrm{control}\kern0.5em \mathrm{intervention}\kern0.5em \mathrm{group}}{\mathrm{Efectiveness}\kern0.5em \mathrm{or}\kern0.5em \mathrm{Utility}\kern0.5em \mathrm{active}\kern0.5em \mathrm{intervention}\kern0.5em \mathrm{group}\kern0.5em \hbox{-} \mathrm{Efectivenes}\kern0.5em \mathrm{or}\kern0.5em \mathrm{Utility}\kern0.5em \mathrm{control}\kern0.5em \mathrm{intervention}\kern0.5em \mathrm{group}}. $$

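### Intervention-group costs are planned over 12 months, but no resource-use data are scheduled after the 6-month follow-up

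*Protocol article*

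**What the plan says.** The economic part of the Statistical analysis section sets the cost horizon: "Resource-use and subsequent costs will be estimated over the 12-month time horizon for the intervention group". Control-group costs are to cover only the 8 weeks of waiting. It then states: "Cost per QALY analysis will be carried out over multiple time horizons (e.g. 8-weeks, 6-months, 9-months and 12-months". The later horizons are presented as a way to show the uncertainty between data observed to week 8 and results extrapolated beyond it.

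Table 2, placed under Dropout measure, gives the collection times. The resource-use row reads "CSRI Resource utilisation BL, Post-T, 6-FU". The row for the first QALY instrument reads "EQ-5D-5 L Health status BL, Post-T, 6-FU, 9-FU, 12-FU", and ReQoL-10 has the same times, "BL, Post-T, 6-FU, 9-FU, 12-FU". The section on the Client Service Receipt Inventory (CSRI) describes its role: "This collects individuals’ use of health and social care resources". It adds that the study site uses this version routinely.

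The only extrapolation described is for the comparator: "extrapolating outcomes from the 8-week time period in the control group to a longer time horizon".

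**The concern.** A cost-per-QALY ratio needs costs and QALYs over the same period. As scheduled, the intervention group's QALYs are measured to month 12, but its use of health and social care is measured only to month 6. The 9- and 12-month cost totals need quantities of resource use that no listed instrument collects.

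This matters because long-term cost-effectiveness is part of the overarching aim in the Aims section and has its own research question and hypothesis. Later service use is also to be expected: the Risk management section says that, after the supported period, scores decide whether a patient is discharged or referred on for further treatment. Any such use after month 6 goes unrecorded. The 12-month ICER and any acceptability curve at £20,000 per QALY would then rest on a cost difference that is partly absent, or filled by a method the article does not state. Resource use not asked about at the time may not be recoverable later.

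**Working it through.** **Inputs**

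- Intervention-group cost horizon: 12 months (Statistical analysis).
- Control-group cost horizon: 8 weeks (Statistical analysis).
- Cost-per-QALY horizons: 8 weeks, 6, 9 and 12 months (Statistical analysis).
- Last scheduled CSRI: 6-month follow-up (Table 2).
- Last scheduled EQ-5D-5L and ReQoL-10: 12-month follow-up (Table 2).
- Assumption: each CSRI recall period reaches back to the previous CSRI. The article does not state the recall period.
- Conversion: 8 weeks / 4.345 weeks per month = 1.84 months.

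**Share of the horizon without scheduled resource-use measurement**

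Uncovered share = (horizon − time of last CSRI) / horizon, horizons counted from baseline.

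*Intervention group, follow-ups counted from baseline (last CSRI at month 6):*
- 6 months: (6 − 6)/6 = 0
- 9 months: (9 − 6)/9 = 3/9 = 33%
- 12 months: (12 − 6)/12 = 6/12 = 50%

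*Intervention group, follow-ups counted from the end of treatment (last CSRI at 6 + 1.84 = 7.84 months):*
- 9 months: (9 − 7.84)/9 = 1.16/9 = about 13%
- 12 months: (12 − 7.84)/12 = 4.16/12 = about 35%

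The article does not define the origin of the follow-up clock outright. The economic text lists 8 weeks, 6, 9 and 12 months as points on one 12-month scale, which favours baseline. The gap remains on either reading.

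*Control group (costs to 8 weeks = 1.84 months):*
- 6 months: (6 − 1.84)/6 = about 69%
- 9 months: (9 − 1.84)/9 = about 80%
- 12 months: (12 − 1.84)/12 = about 85%

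**Does anything else in the article fill intervention-group months 6 to 12?**

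- The data sources cited for costing supply unit costs. These are prices, not quantities of use.
- The planned extrapolation concerns control-group outcomes after week 8, not intervention-group resource use after month 6.
- Multiple imputation cannot recover a variable that is scheduled for no participant at those times.
- The platform logs (Engagement and usage measures) record use of the programme, not of health and social care.
- Routine use of the CSRI at the site is mentioned, but without any collection at 9 or 12 months and without records linkage.

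**Could the CSRI row be shorthand?** Table 2 has a separate code for all follow-ups, and the two rows directly above the CSRI spell out 9 and 12 months. The shorter entry reads as deliberate.

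**After the fix.** With a CSRI at months 9 and 12 and recall to the previous one, the intervention-group uncovered share is 0 at both horizons.

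**The case against.** The strongest reply has four parts.

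1. *This is a condensed article, and the full protocol or analysis plan may name a source for later costs.* That would excuse silence. Here, though, the article states a 12-month cost horizon and a schedule that stops at 6 months, and the two do not fit together. The mismatch stands.

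2. *The 9- and 12-month results do have cost data.* A reader might infer that they have none. That would be wrong: CSRI data to 6 months exist, and delivery cost within the 8-week treatment can be costed from the six planned reviews of 10 to 15 minutes each. What is missing is scheduled resource use after the 6-month CSRI. This part of the reply holds.

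3. *The control arm is the larger limitation.* Waiting-list participants start treatment at week 8 and their costs are planned for 8 weeks only, so every ICER beyond that point already relies on an extrapolated comparator. The article says so openly. This holds too: completing the CSRI would make one arm's costs measured, but would not make the 9- and 12-month ICERs fully observed. It does not excuse leaving the measurable arm unmeasured.

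4. *The main analyses are untouched.* The primary clinical comparison, the sample size and the 8-week economic comparison do not depend on later CSRI data. That is correct and limits the reach of the point.

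A reader might also fault the absence of EQ-5D-5L and ReQoL-10 at 3 months. The documents do not support that as an error: Table 2 and the economic text agree on the times of these measures, the area-under-the-curve method allows unequal spacing, and nothing shows that utility changes fastest between week 8 and month 6.

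**Conclusion.** The mismatch is real. The article plans intervention-group costs over 12 months and cost per QALY at 9 and 12 months, but schedules no resource-use measurement after the 6-month follow-up and names no other source or method. The uncovered part is 3 of 9 and 6 of 12 months (33% and 50%) if follow-ups run from baseline, and about 13% and 35% if they run from the end of treatment. Both sets assume that CSRI recall periods join up without gaps.

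The effect on the ICER cannot be sized. A reader might be tempted to multiply an assumed monthly cost by six and convert it to QALYs at £20,000. The documents give no monthly cost, and the product would be gross cost in one arm, whereas the ICER uses the difference between arms. The direction of any bias is unknown as well.

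Nor should a reader conclude that an observed 6-month ICER would be left once the later horizons are set aside. Control costs are planned for 8 weeks only, so the 8-week comparison is the only one with both arms observed.

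**What to change.** Extend the CSRI row of Table 2 to the 9- and 12-month follow-ups, matching the EQ-5D-5L and ReQoL-10 rows, and state that each CSRI asks about the period since the previous one. Those assessments already take place, so the cost is one table row, a small amendment and a small extra burden on respondents at two contacts.

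If the investigators already intend to take later resource use from service records, the economic section should name that source and the period it covers.

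If the CSRI cannot be added and no such source exists, reword the economic section so that measured intervention-group costs stop at 6 months, and label the 9- and 12-month intervention costs as modelled, with the method stated. This costs only wording, but gives up measured long-term costs.

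Under any of these options, label every ICER beyond 8 weeks as resting on an extrapolated control arm.
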